## 2. OBJECTIVES

The objectives are to examine in a randomized controlled trial whether:

- 1) feedback on relevant daily life person-context interactions (as measured with MET-D) during pharmacotherapy directly affects treatment response in terms of immediate and follow-up decrease of depressive symptomatology and relapse
- 2) feedback on relevant daily life person-context interactions (as measured with MET-D) during pharmacotherapy is cost-effective
- 3) measurement of relevant dynamic daily life behaviours significantly contributes to the prediction of the future course of depressive symptomatology.
- 4) individual differences in (i) the effect of feedback on daily life person-context interaction and (ii) the predictive value of these person-context interactions can be traced back to genetic differences

### 3. STUDY DESIGN

#### Experience Sampling Method (ESM):

ESM is a structured diary method developed to assess subjects in their daily surroundings. This method has been validated for the use of studying the immediate effects of stressors on mood [11, 14, 16]. Most ESM studies use the paper-and-pencil method in answering and registering the ESM questions. Recently our research group has patented an interactive ESM palmtop (the MET-D). The feasibility and validity of computerized ESM has been demonstrated [30]. The MET-D signals subjects at random moments of the day to answer MET-D produced questions about affect and daily events. Answering the MET-D questions after each auditory signal ("beep") will take about 30 seconds, which is far less demanding for the subjects compared to the traditional paper-and-pencil ESM method. The MET-D is programmed to emit 10 times a day a beep at random intervals in each of the ten 90-minutes time blocks between 7:30h and 22:30h, on 5 consecutive days during pre- and post-intervention measurements. Additionally, for the MET-D intervention group, the MET-D will be programmed to emit 10 times a day a beep at random intervals in each of the ten 90-minutes time blocks between 7:30h and 22:30h on 3 consecutive days a week during a 6-week period. After each beep, subjects have to fill out the self-assessment on the MET-D device to record current context (activity, persons present, location, physical activity), stress appraisals of this context, and mood. Mood questions include 4 Positive and 5 Negative Affect items. Examples are 'happy' and 'relaxed' for positive affect and 'depressed' and 'irritated' for negative affect. The self-assessments will be rated on 7-point Likert scales (ranging from 1= 'not at all' to 7= 'very'). Subjects will be instructed to complete the MET-D measurements as quickly as possible after the beep. This emphasis helps to minimize retrospective memory distortion.

#### Design:

A randomized controlled trial will be conducted with three treatment arms:

- The **first** arm ('MET-D intervention *with* feedback'; n=40) receives 5-day pre- and post MET-D assessment *and* continuous MET-D assessment (each week 3-days MET-D measurement during a 6- weeks period) *with feedback* (to both patient and therapist) during treatment as usual (TAU= antidepressant pharmacotherapy). This is the experimental group.
- The **second** arm ('MET-D intervention *without* feedback'; n=40) also receives a 5-day pre- and post MET-D assessment *and* a continuous MET-D assessment (3 days of MET-D measurements during a 6-weeks period) but *without feedback* during treatment as usual (TAU). In order to prevent any effects of different duration of the weekly contacts with the researcher, alternative weekly activities (interviews on anxiety and depression) are carried out. This is the control experimental group.

- The **third** arm (control group; n= 40) receives 5-day pre- and post MET-D assessment but no additional intervention during TAU.

**Feedback:**

Patients in the first arm receive MET-D feedback after each intervention week. This sums up to a total of 6 feedback moments. The MET-D feedback will be given verbally, written, and graphically (in clear pie charts and bar graphs) to both patient and therapist, showing emotional responses to daily life activities, events and social situations and how these daily life situations relate to momentary affective responses of the participant. The researcher will communicate the feedback verbally, according to a standardized protocol, to the patient. The researcher gives the same feedback to the treating therapist (if applicable). The therapist can additionally support the participant in modifying his/her daily life behaviour towards situations of more positive emotions and adjust therapeutic strategy or advice. Patient and treating therapist will receive a written copy of the feedback from the researcher. The feedback will focus on change in positive emotional responses in daily life in order to refocus and redirect the participant towards occasions for emotional strength. The feedback shows the participant's changes in affective responses in daily life situations since the start of the study. In addition, the feedback will show the relationship between (change in) affective responses in daily life and current depressive symptoms. In this way, the patient gets increased control over the cause of his/her depression and is made aware of small improvements.

Examples of what the participant will know after a feedback session:

- The average amount of his/her physical activity in the past days. How it changed compared to the last measurements (did it increase or decrease?). What the relation is between his/her moments of physical activity and the positive emotions generated at those moments. The data may show that the participants receive more positive emotions in moments of more physical activity than less physical activity. The researcher communicates this information in such a way that the participant understands what it means and how it relates to his/her daily life behaviour. Furthermore, the researcher mentions the way the participant can change his/her daily life activities in a way that would lead to more positive emotions ('if you want to train your emotional strength you can try to do more regular physical exercise').
- The average amount of time spent in different kinds of company (partner, friends, colleagues, family, strangers, or alone) in the past days. How the type of company relates to positive emotions generated at that moment. How well the participant can generate positive emotions from social situations he/she rated as pleasant (reward experience) and how this ability changed over time. Again, the researcher communicates the information in understandable language and provides compact advice on how to change behaviour associated with increases in positive

emotions. For example, 'you say you do not feel like meeting people, but your own daily life recordings show that when you are in company you, experience more positive emotions than when alone. Therefore, if you want to train your emotional strength you can try meeting more often with people you like'.

The researcher gives the same feedback to the treating therapist (if applicable). The therapist can additionally support the participant in modifying his/her daily life behaviour towards situations of more positive emotions and adjust therapeutic strategy or advice.

Although the participants respond to the same questions, generated by MET-D, throughout the intervention period, the feedback is built up in three modules:

The first sessions (1 and 2) are focused on daily life activities.

Sessions 3 and 4 are focused on daily life events and how patients deal with things that happen in daily life. In addition, at the end, patients also receive information on their progress in daily life activities as discussed in sessions 1 and 2 (for example, a graph showing how much they changed over the four weeks in positive emotions generated from daily life activities).

Sessions 5 and 6 are focused on social interactions in daily life. Again, at the end, they also receive information on their progress in daily life activities (sessions 1 & 2) and daily life events (sessions 3 & 4) accompanied by visual aids: graphs that show changes over the entire six week intervention period.

There are several reasons why we chose to make three different modules:

- (1). Information on all items at once is too much, with the ensuing risk that participants get confused and do little or nothing with the information. Therefore, information is built up gradually over the course of treatment, while participants get more and more used to the procedure.
- (2). Individuals may habituate quickly (i.e. feel bored) if feedback is received on the same issue over and over again. Now, there are new elements and training possibilities added each two weeks, ensuring "novelty".
- (3). A danger of repeating the feedback on the same items for too long is that the participants get too much insight in the construction of the feedback and will, in the end, fill in socially desired information in their daily life recordings to get positive responses from the researcher. Therefore, feedback is construed differently each two weeks. Since participants will not be informed on future items of feedback they cannot provide socially desired responses. (Another characteristic of the design preventing socially desired responses is that the various feedback results are retrieved through statistical associations between several items which cannot be manipulated readily by participants). Therefore, the study will not formally assess socially desired responding tendencies.

The one constant element of feedback over all six sessions, however, is feedback on the association between patients' average positive emotions as assessed with MET-D and their amount of depressive complaints as assessed with SCL-90 depression scale items (filled in each evening in the MET-D device).

In both treatment arms 1 and 2, participants have weekly sessions with the researcher. In treatment arm 2, however, no feedback on the daily recordings is given. In order to prevent any effects of different duration of researcher contacts in both arms, the difference in time is filled by doing two more interviews on anxiety and depression in treatment arm 2 each week. The structure of the sessions is built up according to a standardized protocol. Clear instructions are formulated on how to give feedback and perform the session in a similar manner for each participant. Training is provided to researchers.

In both arms 1 and 2 there is also a debriefing concerning the MET-D measurements at each session. Discussed are things as: why the participant missed some measurements, whether there are any technical problems, whether some things are unclear etc. Furthermore, the participant is encouraged to fill in the MET-D questions next time as accurately as possible conform the instructions of the researcher.

Levels of reward experience, stress sensitivity and affect variability are calculated from the MET-D observations for each subject at the end of each intervention week. Since these are complex phenotypes derived from combinations of data they are not subject to easy conscious manipulation by patients.

Before entering the study, subjects will be screened for a current depressive episode by means of the Structured Clinical Interview for DSM-IV Axis I Disorders (SCID-I) and the Hamilton Depression Rating Scale (HDRS). After inclusion, a saliva sample will be taken for genetic analysis and the subject has to complete the following measurements: Inventory of Depressive Symptoms (IDS) [31], the NEO personality inventory (NEO-PI-R) [32, 33], Childhood Trauma Questionnaire (CTQ) [34], Interview for Recent Life Events (IRLE) [35], Empowerment Questionnaire [36], TiC-P (Trimbos/iMTA questionnaire for Costs associated with Psychiatric Illness) [37], PRODISQ (PROductivity and DISease Questionnaire) [38], and EQ-5D (Euroqol-5D) [39]. Because we hypothesize that the effect of the MET-D feedback on reward experience results in an increase in of empowerment of the subjects, the Empowerment Questionnaire will be used as an additional measurement of the effect of the MET-D intervention. The latter three questionnaires (TiC-P, PRODISQ and EQ-5D) will be used in the costs-efficacy analysis of the MET-D.

All subjects receive additional MET-D training on a separate moment. All groups receive the following pre and post intervention measurements: i) SCID-I interview for diagnosis of depression, ii) HDRS, and iii) IDS. In addition, there are four follow-up measurements of SCID, HDRS and IDS for all groups at 4, 8, 12 and 24 weeks after the end of the intervention, and two follow up measurements of TiC-P, PRODISQ, and EQ-5D for all groups at 12 and 24 weeks after the intervention (see table 1).

**Table 1: Overview of design of the randomized controlled trial**

| Subjects | Screening | MET-D
Instruction | Pre
5 days | 6 weeks MET-D
intervention 3d/wk       | Post
5 days | Follow Up 4,
8, 12, 24 wks |
|----------|-----------|----------------------|---------------|-------------------------------------------|----------------|-------------------------------|
| n= 40    |           | *                    | MET-D         | continuous MET-D with
feedback + TAU   | MET-D          | —————→                        |
| n= 40    |           | *                    | MET-D         | continuous MET-D
without feedback +TAU | MET-D          | —————→                        |
| n= 40    |           | *                    | MET-D         | TAU                                       | MET-D          | —————→                        |

**Time frame**

[figure not shown]

t number of individual visits for the patient

• SCID-I (after screening: only SCID-I depression), Hamilton Depression Rating Scale (HDRS), Inventory of Depressive Symptoms (IDS), and medication monitor

◆ NEO-PI-R, Childhood Trauma Questionnaire (CTQ), Saliva Sample

P Empowerment Questionnaire

□ Interview for Recent Life Events (IRLE)

▽ TiC-P, PRODISQ, EQ-5D

## 4. STUDY POPULATION

### 4.1 Population (base)

A group of depressive patients (n=140) will be recruited within (i) SEARCH, the research network of mental health institutions within Limburg and South-Brabant, The Netherlands, (ii) general practices and (iii) the general population. The patients will be randomly divided into three groups.

### 4.2 Inclusion criteria

Inclusion criteria are (i) 18-65 years, (ii) a DSM-IV diagnosis of current major depressive disorder or (iii) a past diagnosis of major depression and residual symptoms (HAM-17>7), (iii) current use of antidepressants (all types of antidepressants, thus SSRIs as well as TCAs and MAO inhibitors), (iv) adequate vision, and (v) sufficient Dutch language skills.

### 4.3 Exclusion criteria

Exclusion criteria are (i) diagnosis of non-affective psychosis (e.g. schizophrenia), schizoaffective disorder, or a bipolar disorder, and (ii) current psychotherapeutic treatment.

### 4.4 Sample size calculation

Three groups of 40 patients have been chosen since power calculations showed that these sample sizes using repeated measurements yield around 90% power to examine the main hypotheses with power estimates around 88 and 90%. To detect a 3-point difference in HDRS-17 score between the experimental and non-experimental arms with  $\alpha < 0.05$  and  $\beta < 0.10$  we have a power of 0.93. To detect an effect of reward experience or stress sensitivity (OR=0.5) on future relapse with  $\alpha < 0.05$  and  $\beta < 0.10$  we have a power of 0.95. Since we expect a drop-out of around 20 subjects, we will recruit 140 subjects, leaving 120 participants with complete data randomized over three conditions.

## **5. TREATMENT OF SUBJECTS**

< This chapter is only applicable for intervention studies>

### **5.1 Investigational product/treatment**

The MET-D device is an interactive palmtop that signals subjects at random moments of the day to answer MET-D produced questions about affect and daily events. This new device has recently been patented by our research group and is better equipped than the usual ESM paper-pencil method for the purpose of monitoring since i) it can provide immediate feedback to subjects (it stores all data immediately, can be programmed to perform calculations and to return values to the screen), and ii) it demands less time from subjects to respond to the questions and is therefore more suitable for long-term monitoring.

### **5.2 Use of co-intervention (if applicable)**

Not applicable.

### **5.3 Escape medication (if applicable)**

Not applicable.

## 6. INVESTIGATIONAL MEDICINAL PRODUCT

*<This chapter is only applicable for research with a medicinal product>*

Not applicable.

## 7. METHODS

### 7.1 Study parameters/endpoints

#### 7.1.1 Main study parameter/endpoint

The main objective is to examine if feedback on relevant daily life person-context interactions (reward experience and affect variability as measured with MET-D) during pharmacotherapy results in an immediate and follow-up decrease of depressive symptomatology and relapse and whether this leads to a reduction in health care consumption and costs. Main outcomes therefore are pre – post intervention change in i) depressive symptomatology, ii) ESM phenotypes (reward experience and stress sensitivity), iii) pre – post intervention change on the empowerment questionnaire, and iv) health care consumption and costs. This economic evaluation will involve a combination of a cost-effectiveness analysis (CEA) and a cost-utility analysis (CUA). In a CEA effects are presented in clinical outcomes (in our study decrease depression and relapse). The primary outcomes measure for the cost-utility analysis will be Quality Adjusted Life Years (QALYs), based on the EuroQol utility scores.

Furthermore, to examine whether the effect of the MET-D intervention with feedback leads to a long-term change in above described parameters depressive symptomatology, ESM phenotypes and health care consumption and costs are compared between the three groups on base-line and at 12 and 24 weeks follow up.

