**Objective:**

- (1) Does feedback on continuous monitoring with MET-D during pharmacotherapy result in a better treatment response (immediate and follow-up reductions of depressive symptoms, decreased relapse risk)?
- (2) Is feedback on continuous monitoring with MET-D during pharmacotherapy cost-effective?
- (3) Do measurements of daily life person-context interactions improve the prediction of future courses of depressive symptoms?
- (4) Can individual differences in (1) the effect of feedback on daily life person-context interaction and (2) the predictive value of these person-context interactions be traced back to genetic differences?

**Study design:** Randomized clinical trial with three groups of 40 subjects each (2 experimental groups and 1 control group). The first group receives a 5-day pre- and post MET-D assessment *and* a continuous MET-D assessment (3 days of MET-D measurements during a 6-weeks period) *with weekly feedback* (to both patient and therapist) during treatment as usual (TAU). The second group also receives a 5-day pre- and post MET-D assessment *and* a continuous MET-D assessment (3 days of MET-D measurements during a 6-weeks period) but *without feedback* during treatment as usual (TAU). The third group receives a 5-day pre- and post MET-D assessment but no additional intervention during TAU. This is the control group.

**Study population:** A sample of patients (n=120) with a depressive disorder will be recruited within (i) SEARCH, the research network of mental health institutions within Limburg and South-Brabant, The Netherlands, (ii) general practices and (iii) the general population.

**Intervention (if applicable):** The MET-D is a recently developed wearable interactive palmtop suitable for the Experienced Sampling Method (ESM) to study subjects in their daily life. The intervention group receives feedback on MET-D measurements of reward experience in daily life.

**Main study parameters/endpoints:** The rate of change in reward experience measured with the MET-D, and the change in depression symptomatology measured with the Structured Clinical Interview for DSM-IV Axis I Disorders (SCID-I) and the Hamilton Depression Rating

Scale (HDRS). Reward experience is conceptualised as the degree of positive affect following small positive daily events.

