#### **7.1.3 Other study parameters (if applicable)**

Possible moderators of main study parameter:

- number of previous depressive episodes

- previous stress exposure, measured with the Childhood Trauma Questionnaire and the Interview for Recent Life Events
- personality, measured with the NEO personality inventory

Possible confounders/mediators:

- comorbidity (e.g. substance dependence, personality disorders)
- empowerment, measured with the Empowerment Questionnaire
- medication (type, duration of use)

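### The Summary and Section 7.1.1 name different, unranked main endpoints and no primary contrast, so the error rate of a feedback claim is uncontrolled; empowerment also has conflicting roles

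*Protocol*

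**What the plan says.** The Summary gives the main parameters as "The rate of change in reward experience measured with the MET-D, and the change in depression symptomatology measured with the Structured Clinical Interview" and the HDRS. Stress sensitivity, empowerment and costs are not in it.

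Section 7.1.1 gives a different list: "Main outcomes therefore are pre – post intervention change in i) depressive symptomatology, ii) ESM phenotypes (reward experience and stress sensitivity", followed by "iii) pre – post intervention change on the empowerment questionnaire, and iv) health care consumption and costs". Depressive symptomatology has no instrument attached here, and the four numbered items are not ranked. The same section adds: "The primary outcomes measure for the cost-utility analysis will be Quality Adjusted Life Years (QALYs), based on the EuroQol utility scores". Its objective also covers affect variability and relapse, which the numbered list omits.

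Section 4.4 states one treatment-effect power: "To detect a 3-point difference in HDRS-17 score between the experimental and non-experimental arms", with power 0.93. Its other figure concerns prediction of relapse, and Section 7.1.2 makes prediction of the later course of symptoms secondary. Section 9.2 compares the relevant variables among all three groups and names no primary contrast or time point.

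On empowerment, Section 3 expects feedback to raise it and says "the Empowerment Questionnaire will be used as an additional measurement of the effect of the MET-D intervention". Section 7.1.3 puts "empowerment, measured with the Empowerment Questionnaire" under the heading "Possible confounders/mediators".

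**The concern.** Naming the main endpoint is the protocol's task, and this protocol does it twice with different results. With no ranking, no instrument in 7.1.1 and no primary contrast, whichever variable and comparison turn out favourable could be presented as the main result after the data are seen. The error rate of a statement that feedback works is then not fixed in advance.

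The empowerment conflict raises a different risk. A variable that the intervention is expected to change cannot serve as a confounder of that intervention's effect in a randomised comparison. Adjusting for its post-baseline value could take out part of the effect that the trial is meant to measure.

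**Working it through.** **1. The plan's own figure.** The 0.93 in Section 4.4 cannot be reproduced, because no SD or within-subject correlation is given. Inverting the two-mean normal formula at two-sided 0.05 gives the SD that it would imply for a single measurement: SD = 3 / [(1.960 + 1.476) × √(1/n₁ + 1/n₂)].
- 40 versus 40: 3 / (3.436 × 0.2236) = 3.90.
- 40 versus 80: 3 / (3.436 × 0.1936) = 4.51.

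Which applies is unclear. The Summary counts two experimental groups and one control, whereas Section 3 calls only arm 1 the experimental group. If the 0.93 was meant for 40 versus 80, arm 1 versus arm 2 at the same SD has power Φ(3 / (4.51 × 0.2236) − 1.960) = Φ(1.016) ≈ 0.845. Repeated measures could raise this, so the 0.93 is neither confirmed nor refuted.

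**2. Counting the outcomes.** Section 7.1.1 numbers four items. Splitting the ESM item gives five variables: depression, reward experience, stress sensitivity, empowerment, and consumption/costs. Section 9.2 handles costs by an ICER with bootstrapping and describes no significance test for them, so four variables remain for testing. Six is an upper count, reached by adding to the five (consumption separate from costs, or QALYs).

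**3. Chance of a false result favouring feedback.** Assumptions: no true effect, each test at unadjusted two-sided 0.05, only results in favour of arm 1 counted, and any one of them sufficient. With independent outcomes on one contrast:
- four variables: 1 − 0.975⁴ = 9.6%;
- six variables: 1 − 0.975⁶ = 14.1%.

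For two contrasts, arms 1 versus 2 and 1 versus 3 share arm 1, so a simulation was used (400,000 null draws, three equal arms, common between-outcome correlation ρ). The protocol gives no ρ; the range is assumed.

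| Variables | Contrasts | ρ = 0 | ρ = 0.3 | ρ = 0.5 | ρ = 0.7 |
|---|---|---|---|---|---|
| 4 | 1 v 2 only | 9.6% | 8.7% | 7.8% | 6.5% |
| 4 | 1 v 2 or 1 v 3 | 16.9% | 15.1% | 13.6% | 11.4% |
| 6 | 1 v 2 only | 14.1% | 12.2% | 10.4% | 8.2% |
| 6 | 1 v 2 or 1 v 3 | 24.3% | 20.7% | 17.7% | 14.0% |

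The reference is 2.5% for one test on one contrast in the favourable direction.

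**4. Splitting alpha instead of choosing one outcome.** With the SD of 3.90 from step 1, power is Φ(3.436 − z), where z is the two-sided critical value.
- One outcome at 0.05: 0.93.
- Four outcomes at 0.0125: Φ(3.436 − 2.498) = 0.83; about 54 per arm would restore 0.93.
- Six outcomes at 0.0083: Φ(3.436 − 2.638) = 0.79; about 58 per arm would restore 0.93.

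**5. Empowerment, passages side by side.** Section 3: a hypothesised effect of feedback. Section 7.1.1: a main outcome. Section 7.1.3: possible confounder or mediator. The first two agree with each other and with mediator. They do not agree with confounder.

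**The case against.** The strongest reply is that the protocol nowhere says one positive outcome is enough, ties alpha 0.05 only to the two calculations in Section 4.4, and may leave multiplicity to an analysis plan that is not shown. All of this stands. The absence of an adjustment method is not the finding, and the percentages depend on a claim rule that the protocol does not state. The reply does not remove the two different endpoint lists.

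A reader might infer that a false claim is likely, citing six outcomes on two contrasts: 1 − 0.95¹² = 46%. The documents do not support that. Section 7.1.1 numbers four items; costs go to estimation; the two contrasts share an arm, which lowers the two-sided figure to about 43% even with independent outcomes; and that figure counts results against feedback as well as for it.

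A reader might also infer that adjusting for empowerment produces false positives. It would tend to remove effect instead. Nor is adjustment actually planned: the heading in 7.1.3 includes mediators, and Section 9.3 declares multivariate analysis not applicable. What stands is an inconsistent label that permits a harmful adjustment.

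Finally, reward experience could be discounted because feedback targets it. Section 3 argues that these derived measures are hard for participants to manipulate. That can be debated, but the present point does not rest on it.

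**Conclusion.** The concern holds as an inconsistency within the protocol. The main endpoint differs between the Summary and 7.1.1, neither list is ranked, and no primary contrast or time point is fixed, although only HDRS-17 has a treatment-effect power. If any single outcome could carry the claim, a false result favouring feedback has a chance of about 11–17% with four tested variables and 14–24% with six, on two contrasts and for assumed correlations from 0.7 down to 0. On arm 1 versus arm 2 alone the ranges are about 7–10% and 8–14%. All are well above 2.5% and none makes a false claim likely.

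The empowerment conflict is a separate and smaller matter. It threatens a diluted effect estimate, not a false positive.

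**What to change.** - In the Summary and 7.1.1, name one primary outcome, HDRS-17 change, at one stated time point. Pre to post intervention would match how 7.1.1 defines its main outcomes. Section 7.3 schedules the HDRS both before and after the second five-day period, and more than once before the intervention, so say which readings count.
- Name arm 1 versus arm 2 as the primary contrast. Section 3 matches researcher contact time between these arms, so the contrast isolates feedback. Test arm 1 versus arm 3 next, in fixed order.
- Make the other outcomes secondary, and keep the economic evaluation as a separate estimation analysis, as Section 9.2 already describes it.
- In 4.4, state which arms the 0.93 compares, so that it matches the primary contrast.
- In 7.1.3, list empowerment as a mediator only.

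The cost is mainly rewording, including the main objective in 7.1.1, which now contains costs. A single primary test avoids the power loss of an alpha split. If the 0.93 turns out to refer to pooled arms, the power for arm 1 versus arm 2 must be restated. The small downside is that a positive result on reward experience or empowerment alone could no longer be the main finding.
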